#### Exclusion criteria

Participants with any of the following characteristics/conditions will not be included in the study:Use of probiotics, prebiotics or antibiotics in the past 4 weeks (screened participants that are otherwise eligible may enrol into the study after a 4-week wash-out period).Use of proton pump inhibitors in the last 3 months.Chronic treatment with statins or other drugs with known myotoxicity.Musculoskeletal or other disorder resulting in inability to perform physical function testing.Presence of medical conditions causing secondary sarcopenia.Presence of diseases or disorders that can impact muscle mass.At risk for malnutrition (Mini Nutritional Assessment-Short Form [MNA-SF] ≤ 7).Diagnosed gastrointestinal disease with known association with gut microbiota dysbiosis.Lower or upper extremity fracture within the past 6 months and/or hip replacement surgery within the past 12 months.Myocardial infarction in the past 6 months.Coronary artery disease, peripheral vascular disease, previous stroke, or history of transient ischemic attacks.Uncontrolled hypertension (> 160/100 mmHg).Androgen therapy in males or estrogen therapy in females.Kidney failure.History of cholecystectomy.Blindness.Inability to read or understand English.Unintentional weight loss of 5% or more in the last 30 days or 10% or more in the last 6 months.Known infection with human immunodeficiency virus, hepatitis B virus, or hepatitis C virus.Known or suspected immunodeficiency, as determined by history and/or laboratory/physical examination.Treatment with immunosuppressive therapy, including cytotoxic agents or systemic corticosteroids.Other acute or chronic medical or psychiatric condition that, in the judgment of the investigator, would make the subject inappropriate for entry into this study.Any condition or abnormality that, in the judgment of the investigator, would compromise the safety of the participant or the quality of the study data.Currently enrolled in another clinical study or having participated in another clinical study in the 30 days before the screening visit.Milk or soy allergy.

### Randomization and masking

Participants who fulfil the eligibility criteria and consent to participate will be randomly assigned (1:1) to receive either a synbiotic (intervention) or placebo (control). Randomization will be completed by an independent (unblinded) third party using a random number generator in Microsoft Excel. To perform random allocation, stratified block randomization will be used. The unblinded staff will have no interaction with study participants and will not be involved in the collection or analysis of data. They will assign each participant to one of two intervention groups (synbiotic or placebo) and allocate IP based on stratification factors consisting of gender, age, and handgrip strength (“normal” or “low”, based on EWGSOP2 criteria [8]; men: “normal” ≥ 27kg or “low” < 27 kg and women: “normal” ≥ 16kg or “low” < 16 kg). Stratification data will be collected by blinded study investigators from each participant during their screening visit and will be submitted to the unblinded staff responsible for group allocations.

### Allocation concealment and masking

Intervention and placebo will be matched in appearance, taste and consistency, and will have the same packaging and weight. The unblinded staff will be provided with the code for determining which containers are treatment or control and will label all IP containers for both intervention groups. All study participants and investigative site staff involved in data collection will be blinded to treatment allocation.

### Implementation

Screening, enrolment, confirming eligibility, obtaining consent, and all other data collection and analysis will be performed by investigative site staff who are blinded to treatment allocation. Randomization and treatment allocation will be performed by unblinded study staff who will have no other study involvement.

### Objectives

#### Primary aim

To determine the effect of a synbiotic formulation on indicators of functional performance, balance, and muscle strength.

#### Secondary aim

To determine the effect of a synbiotic formulation on muscle mass and architecture, microbiota composition and diversity and their associated metabolites, and self-reported indicators of sarcopenia.

#### Safety aim

To assess the safety and tolerability of a synbiotic formulation in older individuals.

### Study assessments

Data collection will include Short Physical Performance Battery (SPPB), handgrip strength (HGS), timed up and go (TUG) test, as well as body composition and muscle morphology. These outcomes will be assessed at 4 time points (baseline and weeks 8, 16, and 20). Venous blood will be collected at 4 time points by venipuncture of the median cubital vein after overnight fasting using commercial collection tubes. Two 4.5-mL samples will be taken in EDTA and two 8.5mL SST collection tubes. Samples will be rested for 30 min at room temperature followed by centrifugation at 3000 × *g* for 15 min at 4°C after which serum and plasma will be collected into 0.5mL aliquots and stored at − 80°C until analysis. Participants will be carefully instructed on the procedures for fecal sample collection. Participants will be given stool collection kits at each visit, to be collected at home and returned at the following visit, as described below.

### Primary outcome measure: SPPB

Physical performance will be measured with the SPPB, which is a well-validated and widely used tool [36] that has excellent test–retest reliability and predictive validity [37, 38]. The SPPB measures three components (i) standing balance, (ii) 4-m habitual gait speed, and (iii) repeated chair rises. Each of the three domain scores ranges from 0 to 4 points, yielding a composite score ranging from 0 to 12 points. Higher scores indicate better function. A total score of fewer than 10 points indicates a high risk of frailty and falls [38] and a one-point change is considered clinically meaningful [39, 40]. SPPB component measures will be scored according to Table 1.

**Table 1 Tab1:** Scoring schema for SPPB

**Scoring schema for standing balance**	
**Balance Tests**	**Balance score**
Side-by-side stand	a) Not held for 10 s = 0 points
	b) Held for 10 s = 1 point
Semi-tandem stand	a) Not held for 10 s = 0 points
	b) Held for 10 s = 1 point
Tandem stand	a) Less than 3 s = 0 points
	b) Between 3 and 9.99 s = 1 point
	c) Held for 10 s = 2 points
**Scoring schema for 4 m gait speed**	
Unable or > 60 s	0 points
< 60 s but > 8.70 s	1 point
6.21 s to 8.70 s	2 points
4.82 s to 6.20 s	3 points
< 4.82 s	4 points
**Scoring schema for repeated chair rises**	
Unable or > 60 s	0 points
< 60 s but > 16.69 s	1 point
13.70 s to 16.69 s	2 points
11.20 s to 13.69 s	3 points
< 11.20 s	4 points

For the *balance tests*, participants will be asked to stand unassisted in 3 positions:Side-by-side stand (feet in a side-by-side position);Semi-tandem stand (heel of one foot is beside the big toe of the other foot);Tandem stand (toe of one foot is behind and touching the heel of the other foot).

Participants will be asked to maintain each position for 10 s. If unable, the time achieved will be recorded and the next position will be attempted.

*Gait speed* will be measured as the time taken to walk 4 m (between markers set at 3 and 7 m of a 10 m walking course) at the participant’s usual speed. Assistive devices will be allowed if needed. Gait speed will be calculated as meters per second (m/s) and trained staff will record time to the nearest 0.01 s. The best (fastest) of the two attempts will be included in data analysis. Gait speed is comparable to the full battery for predicting disability [38], and slower gait speeds predict higher rates of frailty and hospitalization [41]. Coleman et al. determined 0.11 m s^−1^ to be a clinically meaningful change [42].

For *repeated chair rises*, participants will be asked to rise from an armless chair, sit back down, and repeat this movement five times as quickly as possible without using their arms [43]. Participants will begin the test with their arms folded across their chest, sitting in a chair with a seat height of 43 cm. Participants will be instructed to stand up completely (defined as an upright trunk with full knee and hip extension), make firm contact when sitting and keep their arms folded across their chest. Time (in seconds) will be recorded, beginning upon the prompt, “go,” and stopping when the participant’s buttocks returned to the seat following the fifth stand [44]. No words of encouragement will be used. Chair stand time has been described as a reliable [45], useful measure of lower leg strength [43], fall risk [46], and balance control [47], and has been shown to complement measures of gait speed when screening for sarcopenia [48].

### Primary outcome measure: handgrip strength

Handgrip strength will be measured using a Jamar analog hand dynamometer (Patterson Medical, Warrenville, IL) with the handle set to position II. Participants will be instructed to grip the device and squeeze as hard as possible with their dominant hand [49]. Three trials will be recorded with participants in a sitting position, elbow by their side and flexed at 90°, forearm and wrist in a neutral position, with shoulder adducted and neutrally rotated, as previously described [50]. The maximum of these values will be used for analyses [51]. Grip strength has been shown to predict future function [52] and has been negatively associated with frailty [53].

### Primary outcome measure: TUG test

The TUG test measures the time (in seconds) taken to stand up from a standard chair, walk to and around a marker placed 3 m away at a comfortable pace, return to the chair and sit back down [54]. Participants will be permitted to use walking aids (if necessary) and will be instructed not to use their arms to stand up. Beginning with the participant seated with their back against the backrest of the chair, timing will commence on the command “go” and will stop when the participant returns fully seated in the back of the chair. The task will be performed twice, with the faster (shorter) time used in data analysis. TUG has been used to examine gait, agility, fall risk, balance, and dynamic (turning) movements in older adults [43, 55–57].

### Secondary outcome measure: body composition

Dual-energy X-ray absorptiometry (DXA) will be used to measure whole and regional body composition, including lean body mass (LBM, g), appendicular lean mass (ALM, g), total and regional body fat mass (FM, %), and fat-free mass (FFM, g). Fasting whole-body scans (GE Healthcare Lunar iDXA, Madison, WI) will be acquired with participants in a supine position on the scanner table, wearing light clothing, with their limbs close to their bodies according to the manufacturer’s protocol. Segmental analyses of the whole body into arm, leg, and trunk segments will be separated with anatomical landmarks by the DXA analysis software. Appendicular skeletal muscle mass (ASMM) will be calculated as the sum of the lean soft tissue mass (LSTM) of both the right and left extremities, with the assumption that all non-bone and non-fat tissue is skeletal muscle [58]. Skeletal mass index (SMI) will be determined as the ALM divided by height squared (kg/m^2^) [59]. Body composition via DXA will be evaluated at baseline and week 16.

Body mass index (BMI), total body and segmental fat percent and weight, total body water percent and weight, total body and segmental muscle mass, and FFM will be estimated using bioelectric impedance analysis (BIA) with a multi-frequency body composition analyzer (Tanita MC-780U, Tokyo, JP) at 4 time points. Impedance will be analyzed in a fasting state, with participants standing barefoot on the electrode platforms, holding grips with both arms straight down at their sides.

### Secondary outcome measure: muscle morphology

Muscle mass and architecture will be quantified via ultrasound examination (Sonosite iViz, Fujifilm, Tokyo, JP) of the *rectus femoris* (RF) and *vastus intermedius* (VI) at 4 time points. Participants will lie supine on an examination table, hips in a neutral position, knees in full extension, ankles at 90°, and both feet on the table, as previously described [60]. The assessed muscles will be in a relaxed state (5 min) to avoid muscle contraction-induced fluid shifts [61], and scans will be obtained before any functional testing [62]. A horizontal reference line will be drawn at 50% of the distance between the greater trochanter and the superior border of the patella of the dominant leg. These anatomical landmarks were chosen based upon guidelines proposed by the SARCopenia through UltraSound (SARCUS) working group of the European Geriatric Medicine Society [60, 63]. With adequate transmission gel applied to the transducer head, two images will be obtained at this point: (i) an image in the transverse plane with the transducer placed perpendicular to the long axis of the thigh, and (ii) an image in the sagittal plane with the transducer placed parallel to the long axis. All images obtained will be subsequently analyzed using ImageJ (NIH) software [64]. Muscle thickness (MT), echo intensity (EI), cross-sectional area (CSA), and subcutaneous tissue thickness (STT) will be measured on the transverse images; fascicle length (FL) and pennation angle (PA) will be measured on the sagittal images [65, 66]. Measurements will be taken three times, and the mean value will be recorded and included in the data analysis [67]. Low levels of muscle mass as determined by the ratio of fascicle length to muscle thickness will be factored to obtain the Ultrasound Sarcopenia Index (USI) [68].

### Secondary outcome measure: fecal microbiota composition and diversity

Stool samples will be collected at 4 time points by participants at home within 72 h of each of their upcoming study appointments. Spontaneously voided feces will be collected into specimen containers, placed within provided biohazard bags, and immediately frozen until transfer to our research site, where they will be stored at − 80 °C until analysis. DNA extraction and 16S rRNA or whole-genome shotgun (WGS) sequencing will be performed to determine α- and β-diversity and taxonomic abundance [69, 70].

### Secondary outcome measure: anthropometric variables

At baseline, body mass will be recorded in light clothing to the nearest 0.1 kg using a digital scale (Tanita, Tokyo, JP). Height (without shoes) will be measured using a stadiometer (SECA 213, Hamburg, Germany). BMI will be calculated as weight (kg) divided by height (m)^2^.

### Secondary outcome measure: calf circumference

A non-elastic tape measure (SECA 201, Hamburg, Germany) will be used to measure calf circumference (CC) at the widest part of the non-dominant leg with participants in a supine position. The tape will be placed flat on the skin, taking care not to compress the sub-dermal tissue. Studies support the utility of CC as a proxy marker for measuring muscle mass [71–73]. CC has shown moderate to high sensitivity and specificity in predicting sarcopenia [74, 75] and predicts disability risk in older adults [76]. CC will be assessed at baseline and week 16.

### Secondary outcome measure: dietary assessment

Habitual dietary intake will be recorded by participants using 3-day dietary intakes for the days leading up to each of the 4 study appointments. Dietary intake data will be analyzed to discern energy intake, and macro- and micro-nutrients. Participants will also complete the Australian Eating Survey [77] food frequency questionnaire at baseline only and before randomization to establish pre-intervention dietary patterns.

### Secondary outcome measure: SARC-F

SARC-F is a recently developed rapid screening tool for sarcopenia [78]. It is a self-reported questionnaire consisting of 5 components: Strength, Assistance with walking, Rising from a chair, Climbing stairs and Falls, respectively. Each of the components is scored from 0 to 2 points, yielding a composite score ranging from 0 to 10 points. Lower scores indicate better function. A total score of ≥ 4 points is indicative of sarcopenia. A recent meta-analysis [79] reported that SARC-F has excellent specificity in screening for sarcopenia, however, due to its low to moderate sensitivity [80], it may detect only severe cases [8]. Participants will complete SARC-F questionnaires at each study visit.

### Safety outcome measures

Serum and plasma samples will be analyzed by an external commercial pathology facility to determine changes (outside normal variation) in clinical chemistry (Comprehensive Metabolic Panel [CMP]) and clinical hematology markers (Complete Blood Count [CBC]) elicited after baseline and through week 16. Adverse events (AEs) and serious adverse events (SAEs) will be assessed and recorded from baseline through week 20.

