#### Safety aims

We hypothesize synbiotic administration will be safe and well-tolerated as defined by the absence of:(10)Changes (outside normal variation) in CBC elicited after baseline and through week 16(11)Changes (outside normal variation) in CMP elicited after baseline and through week 16(12)AEs elicited after baseline and through week 20(13)SAEs until study completion

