### Participant withdrawal and/or discontinuation from the study

Participants will be informed they may withdraw from the study at any time. This will be explained during the consent process and is detailed in the ICF. Participants will be made aware they may be discontinued at any time at the discretion of the investigators for safety reasons, or the inability of the participant to comply with the protocol-required schedule of study visits or procedures. Investigators may discontinue or withdraw a participant from the study for the following reasons:Non-compliance to study protocol.Occurrence of AE related to the intervention, laboratory abnormality, or other medical condition such that participation in the study would not be in the best interest of the participant. This includes whether the participant meets an exclusion criterion (newly developed or not previously recognized).Disease progression requiring discontinuation of the study intervention.

Throughout the duration of the study, the research team will evaluate the well-being of all participants. If continued participation is considered harmful to an individual’s health or safety, that participant will be withdrawn from the study. If a participant is discontinued or withdraws from the study, every attempt will be made to have them complete an Early Termination Visit to determine the participant outcome, to ensure they are withdrawn safely, and to close off any unresolved AEs, if possible. Participants who withdraw after randomization will not be replaced.

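### The safety blood count is assigned to serum and plasma, and no whole-blood sample is described, so safety hypothesis 10 cannot be measured as written

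*Protocol article*

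**What the plan says.** Three places in the protocol article bear on this.

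- **Safety outcome measures** names the specimen and the tests in one sentence: "Serum and plasma samples will be analyzed by an external commercial pathology facility to determine changes (outside normal variation) in clinical chemistry". The sentence goes on to "clinical hematology markers (Complete Blood Count [CBC]) elicited after baseline and through week 16". Serum and plasma are the only specimens named for both panels.
- **Study assessments** describes how blood is drawn and handled at the four time points. "Two 4.5-mL samples will be taken in EDTA and two 8.5mL SST collection tubes". Then: "Samples will be rested for 30 min at room temperature followed by centrifugation at" 3000 × g for 15 minutes at 4 °C, "after which serum and plasma will be collected into 0.5mL aliquots", which are frozen at −80 °C to await analysis. No tube is exempted from this sequence.
- **Safety aims**, under Hypotheses and study endpoints, makes the CBC an endpoint. The product is to be called safe and well tolerated if four things are absent, and item 10 is "Changes (outside normal variation) in CBC elicited after baseline and through week 16".

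Laboratory findings are used elsewhere as well. Safety reporting counts an abnormal laboratory finding as a possible adverse event. The withdrawal section lists among its grounds "Occurrence of AE related to the intervention, laboratory abnormality, or other medical condition".

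**The concern.** A CBC counts red cells, white cells and platelets in whole blood. Serum and plasma are what is left when the cells have been spun out. The article therefore ties a prespecified safety endpoint to a specimen that cannot supply it, and its handling text offers no other specimen.

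At stake is hypothesis 10, and with it part of the article's own definition of safe and well tolerated. The loss cannot be repaired afterwards, because cell counts cannot be recovered from centrifuged aliquots. By the dates under Trial status, recruitment began in November 2022 and the enrolment target was expected to be met in April 2024, so many of the samples concerned may already have been taken.

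**Working it through.** No figure in the plan is in dispute, so the check is to set the passages side by side.

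1. **Endpoint.** Safety aims, item 10, needs CBC values at baseline and afterwards up to week 16.
2. **Specimen named.** Safety outcome measures gives serum and plasma for both the CMP and the CBC.
3. **Specimen available.** Study assessments draws two EDTA and two SST tubes. The EDTA volume is 2 × 4.5 = 9.0 mL, the SST volume is 2 × 8.5 = 17.0 mL, and the total is 26.0 mL per draw. The samples are centrifuged and what is kept is serum and plasma. No volume is left as whole blood.
4. **CBC.** The named specimen (step 2) and the kept specimen (step 3) agree with each other, and neither contains the cells that step 1 requires. Followed literally, the plan yields no CBC.
5. **CMP.** Clinical chemistry can be measured on serum, and serum is kept. Item 11 is not affected by the specimen error.
6. **Extent.** One of the four safety hypotheses (items 10 to 13) is affected, and one of the two laboratory ones (items 10 and 11). It is affected for all of the planned 74 participants, since the same text applies to everyone. A count of lost CBC results would need the CBC visit schedule and the retention achieved. The text gives only a window ending at week 16, the schedule figure is not shown, and the sample-size section allows for about 30% dropout. No count is given here for that reason.
7. **Cost of a repair.** Keeping one of the two EDTA tubes as whole blood uses 4.5 of 9.0 mL, that is 4.5 / 9.0 = 50% of the EDTA blood at that visit. The other EDTA tube is still available for plasma.

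**The case against.** The strongest reply is that this is a slip in one sentence. EDTA tubes are drawn, an external pathology facility is used, and it is quite possible that one tube of each type goes straight to that facility. Safety outcome measures does not say that its samples are the 0.5 mL aliquots held at −80 °C. A journal article also condenses a fuller protocol, and laboratory detail is commonly left to that document.

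Much of this stands, and it limits the point in three ways.

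- A reader might infer that the trial has no CBC data. The documents do not show that. The defect is in the text, and site practice may differ from it.
- A reader might infer from the frozen storage that laboratory abnormalities will be seen too late to act on. The documents do not support this. No date of analysis is given, batching is not mentioned, and the adverse-event and withdrawal sections, if anything, suggest that results are expected during participation.
- A reader might infer that laboratory safety monitoring as a whole fails. It does not. The CMP is unaffected, symptoms are asked about at each visit, adverse events are collected to week 20, and the schedule lists heart rate, blood pressure and gastrointestinal questionnaires.

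The appeal to condensation does not dispose of the remainder. The article does not merely leave the specimen out. It gives tube types, volumes, centrifuge settings and aliquot size, and then states a specimen that is wrong for the CBC.

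**Conclusion.** The point holds in a limited form. Safety outcome measures names the wrong specimen for the CBC, and Study assessments, the only handling text, provides no right one. As written, hypothesis 10 cannot be measured in any participant. The CMP hypothesis and the adverse-event hypotheses are untouched by the specimen error, and no primary or secondary efficacy outcome depends on the CBC.

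This rests on reading the handling paragraph as applying to all blood drawn, which is how it is worded, and on the general fact that a CBC requires whole blood. It does not rest on any assumption about when samples are analysed, and nothing is claimed about delay. Whether data have actually been lost depends on what was sent to the laboratory, which the documents do not say.

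**What to change.** - In Safety outcome measures, replace the reference to serum and plasma with whole blood for the CBC and serum for the CMP.
- In Study assessments, state that one of the two EDTA tubes drawn at each safety-laboratory visit is kept uncentrifuged for the CBC, and separate the safety-laboratory samples from the aliquots stored at −80 °C.
- Make that paragraph consistent with the safety-reporting and withdrawal sections, which rely on laboratory findings.
- Confirm what was sent for participants already enrolled. If whole blood was sent, only the text needs correcting. If it was not, report hypothesis 10 as not assessable for those participants.

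The cost is a change of wording and, if practice has followed the text, a change in tube handling. No extra draw or visit is needed. If no EDTA tube is at present kept as whole blood, up to half of the EDTA plasma per safety-laboratory visit is lost from the frozen store.
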